## Study Participants:

| Group name/description | Data collection method | Age range of subjects | Target number of individuals |
| --- | --- | --- | --- |
| Men in the intervention pilot (texting): A**ssigned texting** | Usability survey, routine VMMC clinical review | 18-65 | 50 |
| Men in intervention group (texting): **Randomized into group** | Interview, routine VMMC clinical review | 18-65 | 361(100 selected for the satisfaction and acceptability questionnaires) |
| Men in control group (routine care): **Randomized into group** | Routine VMMC clinical review | 18-65 | 361 |
| Healthcare workers (VMMC clinicians) | Interview | 18-65 | ~8 |

## Data collection:

**
[figure not shown]
**Sample size: For Objective 1, the RCT will apply hypothesis testing for non-inferiority to examine the outcome of interest: AE rate (moderate or severe) occurring ≤ Day 14. A non-inferiority trial is appropriate as we wish to test our assumption that 2wT with reduced in-person follow-up is as safe (not clinically nor statistically inferior) as routine VMMC [59, 60], but with additional advantages including efficiency and lower direct and indirect costs to providers and patients. The non-inferiority margin, based on statistical and clinical considerations, is the maximum difference between the rate of AEs ≤14 Days in control and 2wT arms where we would conclude that 2wT is not inferior to routine care. We set that margin to 1.6% which would create a non-inferiority cutoff of 2% AEs or less in 2wT. The AE proportion cutoff for 2wT non-inferiority was set at a conservative 2% AEs to match the lower bound of AE rates reported by previous rigorous studies [1-3] and because an AE rate of 2% is regarded as a global standard of VMMC safety [61, 62], including in Zimbabwe [42]. Including a possible 10% LTFU, 361 participants per arm provides 90% power at an alpha of 2.5% to detect AEs greater than the non-inferiority margin of 1.6% (Table 2). We would conclude that 2wT is not inferior if we can rule out an AE rate of greater than 2%.

DATA ANALYSIS:

**For Objective 1**, the 2wT safety outcome of interest is cumulative AE rate (moderate or severe) ≤ Day 14. Incidence of AEs before Day 14 will be extracted from routine VMMC data for both 2wT and control. Incident AEs on Day 14 will be identified, classified, and graded for severity using routine MoHCC protocols [9] and recorded on routine VMMC AE forms. We will compare cumulative rates of any moderate or severe AE ≤ Day 14 between groups using Fisher’s exact test as the expected number of AEs is low. The rates will be calculated per arm as: (# moderate + severe AEs)/ (total # VMMC clients who attend/responded to 2, 7 or 14 Day follow-up visits or texts). Multivariate logistic regression models (any AE v none) will quantify the magnitude of difference, adjusting for any potential confounders. To determine follow-up visit reduction, we will compare the mean number of in-person visits for intervention and control using a t-test. A multivariate linear regression model will further quantify the effect of intervention on visit reduction, adjusting for potential confounders. Secondary outcomes include: AE rates on Day 14, texting response rate, time between 2wT AE text reporting and follow-up, severity of AEs. We will perform appropriate summaries of missing data and LTFU, testing for systematic differences in response by study arm. *We hypothesize that 1) 2wT is non-inferior to routine follow-up for patient safety and that 2) 2wT* *will reduce unnecessary follow-up over standard care.*

**For Objective 2,** 2wT costs, we will calculate the relative costs and outcomes (effects) of intervention versus control, including costs for technology, healthcare worker time, and client considerations (travel, text costs, missed work). We will conduct both activity-based costing from the implementation perspective and from the technology perspective to extrapolate our results as costs that would be incurred by the MoHCC should they elect widespread scale up of 2wT. **Approach for costing.** First we quantify the total direct and indirect costs of 2wT deployment, a method previously used for technology cost assessment in Malawi [47], which includes comprehensive costs from installation and training, routine maintenance, healthcare worker time associated with 2wT, and staff efficiency gains/losses in addition to the direct cost of technology. Second, we will estimate incremental costs (incremental relative to standard practice) for the intervention. This component entails a micro-costing study using activity-based approaches for costs incurred (trainings, VMMC service provision, follow-up) and costs averted (health costs for providers and patients saved by reducing visits), adapting previous VMMC costing estimates [63] for 2017 dollars when appropriate. Cost data will also be collected from the study budget, public health clinic budgets, published government reports, and the health economics literature. Lastly, to estimate the cost savings associated with 2wT over routine VMMC follow-up, we will conduct a time-motion study [64, 65] to quantify time spent for VMMC follow-up, indicating potential time savings for providers and VMMC clients. One trained observer will record VMMC client/provider follow-up interactions for 5 days, recording times and activities using a pre-established checklist and a personal digital assistant (PDA) that assigns start and end times. During these same 5 days, client time from registration through visit completion will be recorded by a second observer. Data will be exported into STATA 12.0 for analysis. The combined, overall costs for the delivery of 2wT in public health clinics will be estimated and compared to standard follow-up. *We hypothesize that* *2wT will reduce the costs associated with VMMC patient follow-up over standard care.*

**For Objective 3,** 2wT acceptability, using study recruitment and enrollment logs in addition to the texting database, we will describe levels of acceptance, participation, refusal and drop-out. We will carry out key informant interviews (KIIs) with up to 8 health care workers to gauge acceptability, satisfaction, identify facilitators and barriers to program success, and ascertain suggestions for intervention improvement. KIIs will be audio recorded and transcribed. Atlas.Ti software will be used to create a spreadsheet of key themes, perceived barriers, and suggested facilitators to the program from KIIs. We will also implement questionnaires at the Day 14 visit with a subset of 100 2wT VMMC clients in the main study who were randomized to texting to gauge satisfaction, estimate direct and indirect costs (time away from work, transportation costs), and ascertain suggestions for intervention improvement. Responses from these brief, self-administered, quantitative surveys with VMMC clients will be entered in Excel and frequencies explored in STATA 12.0. For feasibility, costing data will be combined with usability and acceptability information. These comprehensive data will be discussed at a final stakeholder meeting to disseminate study results, validate interpretations and refine recommendations for future scale up and modification of 2wT in Zimbabwe and beyond. Additional meetings between local researchers and the MoHCC will further determine feasibility for replication and scale-up. *We hypothesize that acceptability, usability, and feasibility will be high, aiding program scalability.*

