# 2. STUDY BACKGROUND, PURPOSE AND SUMMARY

Male circumcision (MC) reduces the risk of female-to-male HIV-1 transmission by up to 60% [1-3]. From 2008-2015, 10.4 million voluntary medical male circumcision (VMMC) procedures were performed [4], falling far short of the 20 million needed to reach the UNAIDS/ World Health Organization (WHO) target of 80% coverage in 14 priority countries by 2016 [5]. Reaching the target could avert 3.4 million HIV infections and save $16.5 billion in HIV-related care through 2025 [6]. Although surgical VMMC has been streamlined and made efficient through operational optimization [7], current VMMC follow-up requires at least one in-person visit within 14 days of MC [8-10]. VMMC program guidelines often require multiple, additional visits over the 42-day healing period. **Severe healthcare worker shortages** [11] **combined with rapidly expanding VMMC programs threaten already overburdened healthcare systems by recruiting workers away from facilities or diverting their efforts from other competing patient care needs**.

In pilot studies and controlled trials in sub-Saharan Africa, surgical adverse event (AE) rates from combined moderate and severe AEs range from 0.5% to 8% with few severe AEs resulting in permanent impairment [1-3, 12-19]. Although AE reporting in field settings is challenging [20-22], AE rates averaged 0.8% (range: 0.4%-4.2%) in all southern African countries from 2010-2012 [23]. These low AE rates correspond to 99% of men healing without incident, leading to millions of healthcare visits conducted without cause and needlessly increasing the workload. For men, these unnecessary visits likely create barriers to care such as transportation costs, wait times, and inconvenience [24-29], potentially reducing VMMC uptake. **Empowering men to seek in-person follow-up care only when needed or desired would decrease the burden for both healthcare workers and patients, thereby improving efficiency and reducing both direct and indirect costs for this critical component of combination HIV prevention.**

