Zimbabwe is primed for this type of mobile intervention. In 2014, Zimbabwe reached about 25% of its 1.3 million VMMC target for 2018 [42]. Although some AE underreporting is possible [42], Zimbabwe’s VMMC program is safe with the national VMMC program’s AE rate of 0.35% [42]. Under the current VMMC Zimbabwe Ministry of Health and Child Care (MoHCC) standards, **1 million additional VMMCs in Zimbabwe will translate into** **more than 2** **million unnecessary follow-up visits.** As each VMMC client likely passes through reception, observation, and examination, **the healthcare workload and time lost for VMMC clients healing without complication is likely several times higher.** Moreover, VMMC staff are MoHCC employees who perform most VMMCs in outreach sites (tertiary clinics, schools, communities). Unnecessary follow-up in outreach sites results in additional days away from routine clinic duties, stretching human resources required for myriad other health needs. While healthcare is strained, mobile technology is advancing rapidly: in 2014 approximately 81% of Zimbabweans had a cell phone [43]. This setting with high, unnecessary in-person VMMC follow-up; healthcare worker shortages; and high cell coverage is ideal to test and evaluate a better, low-cost approach to minimizing the burden on both the healthcare system and VMMC clients.

[figure not shown]

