As a national VMMC implementing partner, the ZAZIC consortium, led by the University of Washington’s International Training and Education Center for Health (I-TECH) and local implementing partners, The University of Zimbabwe(UZ)-University of California San Francisco Collaborative Research Program, Zimbabwe Association of Church-related Hospitals (ZACH), and Zimbabwe Community Health Intervention Research Project (ZiCHIRe), works in partnership with the Zimbabwe MoHCC to implement VMMC services in 10 districts. ZAZIC’s program is highly productive and safe: between July 2015-June, 2016, ZAZIC conducted 47,905 MCs and 45,989 follow-up visits to find 151 AEs, an AE rate of 0.3%[44]. Adherence to follow-up visits, another indicator of program quality [45], was good. Over 95% of men attended both Day 2 and Day 7 follow-up; more than 30% also had a Day 42 visit to verify complete healing [46]. With such high follow-up visits, **even if 20% of men were reviewed on Days 2 and 7 for high sensitivity of AE detection, almost 74,000 in-person visits were unnecessary and could potentially be replaced with 2wT interactions between patients and providers** (Figure 1). ZAZIC continues to rapidly scale up. In ZAZIC’s largest urban district, Chitungwiza, we have reached only 14% of the intended 80% target for 2018 [44], indicating ZAZIC projected exponential increase over the coming 2 years. Greater efficiency would enable more VMMCs.

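### The stated 90% power rests on a normal approximation with about 1.3 expected AEs per arm; a valid non-inferiority test on 325 evaluable men per arm has about 57%

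*Protocol*

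**What the plan says.** The sample size paragraph (Protocol, section 4, Data collection) gives these inputs:

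- Margin and cutoff: "We set that margin to 1.6% which would create a non-inferiority cutoff of 2% AEs or less in 2wT".
- Allowance for loss: "Including a possible 10% LTFU".
- Resulting claim: "361 participants per arm provides 90% power at an alpha of 2.5% to detect AEs greater than the non-inferiority margin of 1.6"%.
- The paragraph closes with a rule on the 2wT arm alone: non-inferiority is concluded if a rate above 2% can be excluded.

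The paragraph refers to Table 2, which is not visible in the text available. The visible text gives neither the assumed control rate nor the formula.

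The background section offers several AE rates. For the national programme: "Zimbabwe’s VMMC program is safe with the national VMMC program’s AE rate of 0.35"%, prefaced by "Although some AE underreporting is possible". For the consortium's own programme: "45,989 follow-up visits to find 151 AEs, an AE rate of 0.3"%. For the region: "AE rates averaged 0.8% (range: 0.4%-4.2%) in all southern African countries from 2010-2012".

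The Data Analysis section chooses Fisher's exact test for the AE comparison because few AEs are expected.

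**The concern.** The protocol treats AEs as too rare for large-sample methods when it chooses the analysis, yet its power figure appears to come from a large-sample formula. With one or two events per arm, the normal approximation to a difference in proportions is poor, and the error runs in the optimistic direction.

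The claim is also worded for the wrong hypothesis. Non-inferiority power is the probability of ruling out an excess as large as the margin when the arms are truly alike. It is not power to detect an excess beyond the margin.

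The 90% tells ethics committees, the DSMB and the Ministry that a truly safe intervention has a 10% chance of failing the primary safety test. If the real chance is over 40%, an inconclusive result is nearly as likely as a conclusive one, and readers who trusted the 90% could take it as a sign of harm. The trial also adds an in-person Day 14 review in both arms. If that finds more AEs than routine reporting does, power falls further.

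**Working it through.** **Inputs.** Margin 0.016, cutoff 0.02, alpha 0.025 (taken as one-sided), power 0.90, 361 per arm and 10% loss, all from the sample size paragraph. The rate is inferred: 0.02 − 0.016 = 0.004, assumed equal in both arms. Evaluable men: 361 × 0.9 = 325 per arm.

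**Step 1: reproduce the protocol's figure.** Unpooled normal formula:

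n = (1.960 + 1.2816)² × 2 × 0.004 × 0.996 / 0.016² = 327.04, rounded up to 328. Then 328 × 1.10 = 360.8, or **361**.

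Power by the same formula at 325: 0.016 / √(2 × 0.004 × 0.996 / 325) − 1.960 = 3.231 − 1.960 = 1.271, which is 89.8%. The programme rates of 0.35% and 0.3% give 316–319 and 271–274 per arm after inflation, so they do not reproduce 361.

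**Step 2: event counts.** Expected AEs per arm: 325 × 0.004 = 1.3. Chance of none: 0.996³²⁵ = 0.272. Binomial probabilities for n = 325, p = 0.004:

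| AEs | 0 | 1 | 2 | 3 | 4 | ≥5 |
|---|---|---|---|---|---|---|
| Probability | 0.2718 | 0.3548 | 0.2308 | 0.0998 | 0.0323 | 0.0105 |
| Cumulative | 0.2718 | 0.6266 | 0.8574 | 0.9572 | 0.9895 | 1 |

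**Step 3: exact power of a valid test.** The Farrington–Manning score test at one-sided 2.5% declares non-inferiority at n = 325 only if the 2wT AEs do not exceed:

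| Control AEs | 0 | 1 | 2 | 3 | 4 | 5 |
|---|---|---|---|---|---|---|
| Most 2wT AEs allowed | 0 | 1 | 1 | 2 | 3 | 3 |

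Power is the sum over control counts of P(control count) × P(2wT count within the limit):

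0.2718 × 0.2718 + 0.3548 × 0.6266 + 0.2308 × 0.6266 + 0.0998 × 0.8574 + 0.0323 × 0.9572 + about 0.0101 (five or more control AEs)

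= 0.0739 + 0.2223 + 0.1446 + 0.0856 + 0.0309 + 0.0101 = **0.567**.

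One AE on 2wT against none on control fails, and so does two against two. Both are ordinary results at 0.4%.

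**Step 4: other tests and assumptions** (equal true rates, margin 1.6 points).

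| Test | n per arm | True rate | Power |
|---|---|---|---|
| Score | 325 | 0.3% | 62% |
| Score | 325 | 0.35% | 59% |
| Score | 325 | 0.4% | 57% |
| Score | 325 | 0.8% | 44% |
| Score | 325 | 2% | 27% |
| Newcombe interval | 325 | 0.4% | 56% |
| Exact unconditional | 325 | 0.4% | 57% |
| Score | 361 | 0.4% | 69% |
| Wald | 325 | 0.4% | 87% |

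At 325 per arm the maximum type I error of the score, Newcombe and exact unconditional tests is 2.3–2.4%, so they hold the nominal level. The Wald test does not: its error is 5.25% at 0.4% control and 2.0% 2wT, and up to 10.7% over control rates from 0 to 2%. It allows two 2wT AEs against none on control because the interval is too narrow at such counts.

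**Step 5: the rule on the 2wT arm alone.** An exact one-sided 2.5% test against 2% allows at most 1 AE at n = 325, since P(X ≤ 1) = 0.011 at 2% and P(X ≤ 2) = 0.042. Power at 0.4% is 0.6266, or 63%. At n = 361 it allows 2 AEs (P = 0.024 at 2%), and power is 82%.

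**The case against.** - **The sum was done correctly.** The standard formula gives 361 and 90%. That is true: the fault lies in the method, not in a slip of arithmetic. The stated power is still wrong for any test that holds 2.5%.
- **Table 2 is not visible.** It may state the rate, formula and test. That stands as a caveat. The exact match to 361 makes the inference strong, but it remains an inference. The visible text also does not say where 0.4% comes from. It lies above both programme rates and at the bottom of the regional range, so the remark on under-reporting cannot be tied to it directly.
- **More than 325 may be evaluable.** The denominator counts any Day 2, 7 or 14 contact, and the programme reports over 95% attending both Day 2 and Day 7. This is fair. Power is a step function of n, running from about 56% to 69% between 325 and 361, and it does not approach 90%.
- **The 2% rule is kinder.** With all 361 analysed it gives 82% at 0.4%, 87% at 0.35% and 90% at 0.3%. The gain appears only near full retention: at 350 men, 1 AE is still the limit and power at 0.4% is 59%. This rule also ignores the control arm, so it is not the between-arm comparison that the margin defines.
- **The choice of test may be left to a SAP.** It may, but no test choice rescues the stated figure at the implied rate.
- **The wording on detecting is loose, not wrong.** The paragraph's last sentence does speak of ruling out. This part is minor.

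**Conclusion.** The concern holds. At the rate implied by the protocol's own margin and cutoff, 325 evaluable men per arm give about 57% power with a valid two-arm test, and 361 give about 69%. The stated figure is 90%. The risk of failing to show non-inferiority when the arms are truly equal is about 43%, or 31% with complete follow-up, against the implied 10%. No valid rule examined reaches 90% at 0.4%, including the rule on the 2wT arm alone (63% to 82%). If the true rate is 0.8%, the regional average quoted in the background, score-test power at 325 is 44%.

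This rests on a common true rate of 0.4%, one-sided alpha of 2.5%, a margin of 1.6 points on the risk difference, and 10% loss. The rate and the formula are inferred because Table 2 cannot be seen.

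**What to change.** Keep 722 men and replace the power sentence with wording such as:

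> With 325 evaluable men per arm and a true AE rate of 0.4% in both arms, a one-sided 2.5% score test has about 57% power (69% if all 361 per arm are analysed) to rule out an excess of 1.6 percentage points. Power is about 44% at a true rate of 0.8% and 27% at 2%.

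State the assumed rate and its source in the text, and name the test used for the calculation. If another test that holds 2.5% is preferred, recompute the figures for it. If the rule on the 2wT arm alone is kept as a decision rule, give its power as well (63% at 325, 82% at 361, for a rate of 0.4%).

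This costs wording only. No men are added and care does not change, but the stated power becomes less favourable. If 90% is required, the score test needs about 565 evaluable men per arm, or 565 / 0.9 = about 628 randomised per arm. That is a decision on resources for the sponsor.

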## Study Procedures:

Participant overview:

- 50 men for the pilot. Not randomized. Enrolled into texting. Not included in outcome analysis.
- 722 men in the full study randomized in a 1:1 ratio of texting and control for 361 men in texting and 361 in control (routine care).
- Same recruitment, consent, and follow-up procedures in pilot and intervention as outlined, per group, below

Recruitment and Informed Consent: Each site will establish local recruitment and screening methods that operationalize protocol-specified requirements for eligibility determination in a manner that is tailored to and most efficient for the local study setting and target study population. In brief, information about the study will be disseminated through the Zimbabwe Ministry of Health and Child Care (MoHCC), ZAZIC, and HCW at the selected sites. VMMC demand creation as part of routine ZAZIC program practice will support study recruitment. HCW recruited for participation in the study will be reached at their workplaces (the health care facilities) following communication between the study team and the site leadership. VMMC clients will be recruited in the VMMC clinic area. Recruitment will be managed by a specifically-trained research coordinator. This research coordinator will meet with VMMC patients to sensitize them about the opportunity to participate in a study of text-based follow-up; those meeting eligibility criteria will be individually informed by 2wT staff about the opportunity to participate in the study. Interested patients will be referred to the site study coordinator for study enrollment and informed consent. This person will meet with patients in a private setting, further explain the study, confirm study eligibility, and seek informed consent. Participants who refuse to enroll in the study will be asked to provide informed consent for data collection about reasons for non-participation.

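### The protocol states two non-interchangeable success rules for safety: a between-arm difference below 1.6 points, and a two-way texting AE rate shown not to exceed 2%

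*Protocol*

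**What the plan says.** Both rules stand in the sample-size paragraph of the Protocol, section 4, Data collection.

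- **Difference rule.** The non-inferiority margin "is the maximum difference between the rate of AEs ≤14 Days in control and 2wT arms", and its value is 1.6%.
- **2% rule.** The paragraph links the two: "We set that margin to 1.6% which would create a non-inferiority cutoff of 2% AEs or less in 2wT". It then gives 2% a rationale of its own, as the lower end of AE rates in earlier rigorous studies and as a recognised safety standard for circumcision programmes. The closing decision sentence reads "We would conclude that 2wT is not inferior if we can rule out an AE rate of greater than 2" per cent. Control does not appear in it.

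The paragraph claims that "361 participants per arm provides 90% power at an alpha of 2.5" per cent against the 1.6% margin, allowing for 10% loss to follow-up. The Data Analysis text for Objective 1 compares the arms with Fisher's exact test. That test uses neither the 1.6-point margin nor the 2% bound. No sentence says which rule governs, or that both must be met.

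**The concern.** A difference rule judges two-way texting (2wT) against the randomised control arm. A 2% rule judges the 2wT arm alone. The step from one to the other assumes that control is a fixed 0.4%. In the trial, control is an estimate with its own sampling error, and its true rate need not be 0.4%. The protocol's own background rates are 0.3% (the ZAZIC programme), 0.35% (the national programme) and 0.8% with a range of 0.4% to 4.2% (southern Africa). The added Day 14 review of all participants could also raise the recorded rate in both arms.

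With a handful of events expected, one or two AEs can split the two verdicts. This is the primary safety conclusion of an unblinded trial meant to inform scale-up, so the rule should be settled before the data are seen.

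**Working it through.** **Inputs.** Margin 1.6 points, cutoff 2%, alpha 2.5% (taken as one-sided), power 90%, 361 per arm, 10% loss to follow-up: all from the sample-size paragraph. The control rate of 0.4% is derived as 2.0 − 1.6, because Table 2 is not visible. Evaluable men per arm: 361 × 0.9 ≈ 325.

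**1. Which rule gives 361?** For the difference rule with 0.4% in both arms, by the normal approximation:

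n = (1.960 + 1.282)² × 2 × 0.004 × 0.996 / 0.016² = 327.04, so 328 per arm.

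328 × 1.1 = 360.8, so 361, the stated figure. (Dividing by 0.9 gives 365.) Power at 325: the standard error is √(2 × 0.004 × 0.996 / 325) = 0.00495, and Φ(0.016/0.00495 − 1.960) = 89.8%. The stated size therefore comes from the difference rule.

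For the 2% rule, a one-sample test of 2% against 0.4%:

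n = [(1.960 × √(0.02 × 0.98) + 1.282 × √(0.004 × 0.996)) / 0.016]² ≈ 494 evaluable men.

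**2. Power of the 2% rule at the planned size.** Exact (Clopper-Pearson) upper 97.5% limits at 325 are 1.13%, 1.70% and 2.21% for 0, 1 and 2 AEs, so the rule passes only with 0 or 1 AE. At a true 0.4%, P(X ≤ 1) = 0.996³²⁵ + 325 × 0.004 × 0.996³²⁴ = 62.7%. At 361 evaluable, 2 AEs also pass (limit 1.99%), and P(X ≤ 2) = 82.3%.

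**3. How often do the verdicts differ?** Both binomial arms were enumerated exactly. The difference rule is an upper 97.5% limit for 2wT minus control below 1.6 points (Wald, Newcombe or Farrington-Manning). The 2% rule is an upper 97.5% limit for the 2wT rate below 2% (exact or Wilson, and Wald when paired with Wald).

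| True rate in both arms | Opposite verdicts, 325 per arm | Opposite verdicts, 361 per arm |
|---|---|---|
| 0.4% | 8.6% to 24.5% | 5.3% to 15.0% |
| 0.8% | 13% to 38% | 11% to 24% |
| 2% | 22% to 31% | 26% to 34% |

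With Farrington-Manning and exact limits at 325, the shares are 13.4%, 20.0% and 25.5%. At a true 2% and 325 per arm, the difference rule passes 27% (Farrington-Manning) or 32% (Wald), and the exact 2% rule passes 1%. Pairing a score limit for the difference with a Wald limit for the rate was left out as an unlikely choice. It moves the shares up at 0.4% and down at 2%, but does not remove the disagreement.

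**4. One concrete outcome: 4 AEs in control, 3 in 2wT.** At 325 per arm the observed difference is −1/325 = −0.31 points.

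- Wald upper limit: −0.31 + 1.96 × √(0.00923 × 0.99077/325 + 0.01231 × 0.98769/325) × 100 = −0.31 + 1.59 = 1.28 points. Passes.
- Farrington-Manning upper limit: 1.59 points. Passes narrowly.
- Exact upper limit for 3/325: 2.67%. Fails the 2% rule.

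The same split occurs at 361 per arm under both difference methods. Two-way texting had fewer AEs than control and still fails the closing sentence. Two limits apply at 325: Newcombe gives 1.60 and sits on the boundary, and a Wald limit for the rate, 0.923 + 1.96 × √(0.00923 × 0.99077/325) × 100 = 1.96%, would pass.

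**The case against.** The best counter-reading is that there is one rule stated twice. The text says the margin "which would create a non-inferiority cutoff of 2% AEs or less in 2wT", so 2% can be taken as shorthand for control plus 1.6 points. The closing sentence follows directly on a power statement about the margin, and the objectives, hypotheses and analysis text are all comparative. Table 2 and the statistical analysis plan, neither of which was available, might name the governing rule.

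Part of this stands. The design does point to the difference rule. But the shorthand works only for a known control rate of 0.4%, the 2% has its own absolute-safety rationale, and the closing sentence is worded as a decision rule. An analysis plan could follow either sentence and claim to match the protocol.

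Three stronger readings are tempting and are not supported.

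- A reader might infer that the rules are incompatible. They are not: a trial can satisfy both, and when control is truly 0.4% and 2wT truly 2% they disagree in only about 1% to 6% of trials at 325 per arm, since both usually fail.
- A reader might infer that the 2% rule generally clears a 2wT arm that the difference rule does not. With 0 AEs in control and 1 in 2wT, this happens at 325 per arm under Farrington-Manning (1.72 points against 1.70%). It disappears with a Wald limit (0.91 points) and at 361 per arm (1.55 points).
- A reader might infer an intention to choose the rule after seeing the data. Nothing in the document shows that; the text only leaves the choice open.

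The objection that the shares depend on interval method is also correct, which is why ranges are given.

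**Conclusion.** The point holds as a conflict between two success criteria that are different and not interchangeable. It is more than loose wording, because the choice changes the primary conclusion in roughly 9% to 25% of trials at the design rates with 325 evaluable per arm, 5% to 15% at 361, and 22% to 31% if both arms truly run at 2% (325 per arm). The stated 90% power belongs to the difference rule. The exact 2% rule has about 63% at 325 and 82% at 361.

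These figures assume a design rate of 0.4% in both arms (derived, not read from Table 2), one-sided 2.5% confidence limits for both rules, and the interval methods listed. The protocol fixes none of these methods. If the 2% rule were read as a bare point estimate of 2% or less, disagreement at the design rates with 325 per arm would be 12.8% to 43.2%, depending on the limit used for the difference.

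**What to change.** 1. Replace the closing sentence with one confirmatory rule: non-inferiority is concluded if the upper limit of the two-sided 95% confidence interval for the 2wT rate minus the control rate is below 1.6 percentage points. Name the interval method, for example Farrington-Manning or Miettinen-Nurminen.
2. In the Data Analysis text for Objective 1, align the Fisher's exact comparison with that rule, so that it is not taken as the non-inferiority test.
3. Report the 2wT rate with its exact 95% interval against the 2% benchmark as supportive.

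**Cost.** A few sentences in two places, and no change to conduct. There are two consequences. First, the method must be named because it matters: at 0.4% in both arms and 325 per arm, the difference rule passes 57% of trials by Farrington-Manning and 87% by Wald. The 90% power statement rests on the normal approximation and should be restated for the method chosen. Second, 2% is no longer a formal hurdle. If the sponsor wants to keep it as one, the protocol should say that both criteria must be met and give the power for the joint rule, which cannot exceed that of the weaker component.
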